**9.5 Follow up period (visits 12, 13)**

The follow up period will be (Visits 12-13), on months 8, and 10. The TCV treatment protocol will be performed as follows:

- Neurological assessment will be performed at months 8, and 10,. The Examining Physician **should not** refer to previous neurological assessments carried out on the patient, prior to the completion of the visit’s neurological assessment;
- Documentation and follow-up of each exacerbation will be conducted through the study period.
- Adverse events will be followed carefully at each visit by the Treating Neurologist.

The injection site on the patients arm will be covered by bandage before the examination. Thus, the evolution will not be biased by differences between the placebo and the TCV at injection site.

- 1. **Termination (visit 14)**

The termination visit will include the following procedures:

- Physical examination;

- Vital signs;

- Clinical laboratory evaluation, routine hematology, blood chemistry, and urinalyses will be performed;

- Adverse experiences;

- Concomitant medication;

- Complete neurological examination including FS, AI, EDSS, 10 Meter Walking Test, 9-Hole-peg test, PASAT cognition test.

- Evaluation of relapse;

- MRI

- Termination of double blind phase procedures;

- If an AE is present at the last follow-up visit, it will be followed until the medical condition returns to baseline or is considered stable or chronic

The injection site on the patients arm will be covered by bandage before the examination. Thus, the evolution will not be biased by differences between the placebo and the TCV at injection site.

**9.7 Study Conclusion**

**9.7.1 Completed Patients**

A patient who has met eligibility criteria, has been assigned to a treatment group and has completed 56 weeks of double-blind treatment, is defined as a completed patient

**9.7.2 Premature Discontinuation of Treatment**

The CRO and the local Ethic committee should be contacted by the investigator if a patient prematurely terminates the study.

Premature termination is any withdrawal from the study prior to the scheduled termination visit.

**9.7.2.1 Study Premature Discontinuation Criteria**

- Patient with any clinical intolerable adverse experience/event; **(of grade III or IV) according** to the WHO classification and, in particular, in case of a severe manifestation of hypersensitivity consecutive to a vaccine injection, or of a severe alteration of renal and/or hepatic functions (creatinine clearance lower than 70 ml/min. and ASAT and/or ALAT transaminases higher than 6 times the normal value.
- Patient’s decision to discontinue treatment.
- Initiation of treatment with any other investigational agent;
- Pregnancy’
- Lost to follow-up;
- PI’s decision to prematurely terminate the study for safety or any other reasons.

**9.7.2.2 Follow up of Premature Discontinued Patients**

- Every attempt will made to follow a patient who prematurely discontinued the study until final planned termination visit.
- Any subject who manifests a severe degree of intolerance to the treatment will prematurely discontinued at the discretion of the treating physician, should remain under medical observation as long as deemed appropriate.
- Laboratory tests demonstrating clinical significant changes, should be reported and followed-up until they return to normal or baseline levels. If an AE is present at the last followed-up visit, it will be followed until the medical condition return to baseline or is consider stable or chronic.

1. **T-CELL VACCINATION SUPLLIES**

The T-cells vaccine will be derived form the patient's blood. Each injection will contain specific dead T-cell (10x 106 cells for each specific line) anti PLP, MBP or MOG peptides in 1.5-3 ml saline. For each patient their will be two injection that will be administrated to the patients both arms. The T-cell lines that are specific to peptides derived from MBP will be merged to one injection and the lines that react to MOG or PLP peptides will pooled to the second injection.

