**Appendices**

**APPENDIX I Relapse Definition**

**APPENDIX II Instructions for Testing Lower Extremity Function: Timed 10 Metter Walk**

**APPENDIX III Ambulation Index**

**APPENDIX IV Magnetic Resoncance Imaging (MRI) Protocol**

1. **Protocol SYNOPSIS**

| **Protocol Number** | 02 |
| --- | --- |
| **Study Title** | Single site, Randomized, Double-blind, Placebo-Controlled Study to Evaluation the Efficacy, Tolerability and Safety of PLP, MBP, MOG peptide-Specific T-cell Vaccine **Subcutaneous** Administered in Relapsing Progressive Multiple Sclerosis |
| **Participating Country** | Israel |
| **Clinical Phase** | Phase I/II |
| **Study Objectives** | To compare the efficacy, tolerability, and safety of PLP, MBP, MOG peptide-specific T-cell Vaccine (10-50 x106 cells) injected subcutaneous four times (day zero and after 30, 90,180 days) vs. placebo. |
| **Study Population** | Relapsing Progressive Multiple Sclerosis patients  R-P MS |
| **Study Design** | Single site, Randomized, Double-blind Study comparing MBP, MOG-peptide Specific T-cell vaccination vs. placebo in Relapsing Progressive Multiple Sclerosis patients.  Eligible patients will be randomized to one of the following groups:   - 10-50 millions dead-autologouscell vaccine. - Matching placebo   Patients will be evaluated in the study center for screening at baseline and then after 1, 3, 6, 8, 10 ,12 month for safety evaluation or neurological exams.  All patients will be MRI monitored at baseline and at study completion.  The data will be monitored by CRO.  The recruitment phase is estimated to be 20 month the treatment and monitoring each patient will be 14 month and the overall duration of the study will be 42 month.  The final analysis will be conducted after all patients complete the 14 month period, and will include all pre-defined end-points. |
| **Number of Patients** | 30 patients |

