**Preparation for injection**

1

0-50 million cells in 1-3 ml saline

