Cell preparation and cell proliferation**:** 50 ml of peripheral blood will be drawn from MS patients, supplemented with 10 IU/ml heparin. Peripheral blood mononuclear cells (PBMC) will be isolated by Ficoll Paque (Pharmacia Biotech, Uppsala, Sweden) density centrifugation. Cells will be washed with RPMI with autologous serum. The culture medium contains RPMI supplemented with 1% sodium pyruvate, 1% l-glutamine (200 mM each), gentamicin (20µg/ml) and 2% Hepes (1 M, pH 7.3) (Biological Industries, Kibbutz Beit Haemek, Israel). PBMC will be plated in 96 well round-bottomed micro plates (Falcon, Lincoln Park, NJ., USA) at a cell concentration of 2x105 cells/ well. Each well will contain 100 µl of 2x106 cells/ml and 100µl of medium with twice the recommended antigen concentration. The above assay will be performed in replicates of five. Five wells with cells and medium without antigen will be incubated as a background control. The antigens that will be used in the proliferation assay and their final concentrations are: PHA (Murex Diagnostic Ltd. England) 0.3 µg/ml; tetanus toxoid (Connaught Lab. Inc. Pen. USA) 5 µg/ml; *Candida albicans* (Miles, WA. USA) 20 µg/ml; PPD (Statens Institute, Denmark); synthetic peptides of the human PLP 41-58, 184-199, 190-209, MBP 83-99, 87-110 and 151-170 and MOG 6-26, and 34-56 (obtained from Chiron, produced in a GLP facility that has been approved by the US Institutional Review Boards for use in clinical study identical to this protocol), 5-20 µg/ml. The plates will be incubated at 37oC in a 5% CO2 humidified incubator. After seven days, cell proliferation will be assayed by 3H-thymidine incorporation to DNA determined using scintillation liquid in λ-particle counting (Packard model 2000 counter reader). Radioactive counts per minute (cpm) will be compared between cells cultured with or without the antigens. The proliferation values will be represented as a stimulation index value (S.I.), *i.e*. cpm with antigens divided by the cpm without the antigen (cpm below 300 will not be considered). S.I. values greater than or equal to 2 will be considered to be positive. Positive patients to PLP, MBP and/or MOG will be considered as fulfilling one of the inclusion criteria's.

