**9.4 Treatment Period (visits 8-11).**

The treatment period will include 4 visits (Visits 8-11), on day 1 (first injection) and months 1, 3, and 6. Following the first injection of the TCV (visit 8) there will be additional 3 boosts of the TCV that will be schedule to month 1, 3, 6 (visits 9, 10, 11). Two subcutaneous (S.C.) injections (1.5-3 ml of dead cell preparation) will be prepared each time: one for each arm and each will contain a mixture of lines specific for one protein. For the schedule of injections and visits, see the following table:

| **Visit** | **Injection #** | **Day #** | **# of Fixed Cells** |
| --- | --- | --- | --- |
| **8** | **1** | **1** | **10-50 x 106** |
| **9** | **2** | **30** | **10-50 x 106** |
| **10** | **3** | **90** | **10-50 x 106** |
| **11** | **4** | **180** | **10-50 x 106** |

In addition the patients will be examined.

- Neurological assessment will be performed at months 1, 3, and 6. The Examining Physician **should not** refer to previous neurological assessments carried out on the patient, prior to the completion of the visit’s neurological assessment;
- Routine hematology, blood chemistry, ad urinalyses will be performed at months 6 (visit 11).
- Documentation and follow-up of each exacerbation will be conducted through the study period.
- Adverse events will be followed carefully at each visit by the Treating Neurologist;

The injection site on the patients arm will be covered by bandage before the examination. Thus, the evolution will not be biased by differences between the placebo and the TCV at injection site.

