**10.3 Cell inactivation**

One day prior to the injection date, if indicated by the results of functional tests, the cells will be washed and incubated in culture medium at 10-15 x 106 cells/ml irradiated at 6,000 RAD and then resuspended in 1 ml of PBS or saline and stored at 4oC.

10.4 The following characteristics of these PLP, MBP and MOG peptide-reactive T-cell lines will be evaluated prior to the injection:

1. Expression of TCR ab or TCR-gd and CD4 or CD8 by flow cytometry.

2. The fine specificity of the T-cell lines will be examined in a proliferation assay (18), including PLP, MBP and MOG peptides as described above (see screening procedure).

3. Determination of cytokine profile; the presence of IL-2, IL-4, IL-10, IFN-g and TNF-a in the supernatants of unstimulated and antigen-activated (with PLP, MBP and MOG peptides) will be analyzed by sandwich ELISA (19).

4. Quality Control (QC) tests for microbiological, mycoplasma and endotoxin contaminations will be performed 2-3 days prior to injection.

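### The 10–50 million cell dose fits the per-line rule only up to five T-cell lines, and syringe content and volume are stated inconsistently whatever the line count

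*Protocol*

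**What the plan says.** **Dose.** The Protocol synopsis (Study Objectives) describes a "T-cell Vaccine (10-50 x106 cells) injected subcutaneous four times". The section 9.4 table has one row per dosing visit (visits 8 to 11), each with one injection number and 10–50 million cells.

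**Per-line rule.** The opening paragraph of section 10 (T-Cell Vaccination Supplies) says: "Each injection will contain specific dead T-cell (10x 106 cells for each specific line"). It states no limit on the number of lines. The screening antigens in section 9.1 are "synthetic peptides of the human PLP 41-58, 184-199, 190-209, MBP 83-99, 87-110 and 151-170 and MOG 6-26, and 34-56", which is three PLP, three MBP and two MOG peptides.

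**Frozen stock.** The vaccine preparation flow chart freezes 10 million cells per vial in 3–15 aliquots and marks three injections of frozen cells at visits 9–11. Section 10.2 also gives 10 million cells per vial.

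**Syringe content.** Section 9.4 prescribes two syringes at each visit, "one for each arm and each will contain a mixture of lines specific for one protein". Section 10 also prescribes two, with the MBP lines in one, and then says "the lines that react to MOG or PLP peptides will pooled to the second injection". Under section 9.1, reactivity to PLP, MBP and/or MOG satisfies the inclusion criterion, so one protein is enough.

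**Volume.** The synopsis (Treatment Arms) puts the whole 10–50 million cells in 1.5–3 ml saline, and the placebo in 1.5–3 ml saline. Section 10 puts 1.5–3 ml in each injection and prescribes two. The preparation chart gives 1–3 ml.

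**The concern.** The word *injection* is used in two senses: a dosing visit (section 9.4 table) and one of two syringes at that visit (section 10). The dose is also built in two ways: as a fixed range, and as 10 million cells multiplied by an unlimited number of lines. Staff working from different sections could prepare different cell numbers, syringe contents or volumes for the same patient, each in line with the text they read.

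This is a phase I/II trial in which the adverse-event profile is a primary endpoint. Its results will be reported as those of 10–50 million cells per dosing visit. If the Protocol's own preparation rule can produce a dose above that range, or leaves open what a syringe holds, the safety and efficacy results of the patients concerned do not belong to the treatment as described.

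**Working it through.** **1. Reproduce the stated vial count.** Inputs: 10–50 million cells per visit (synopsis, section 9.4), three frozen boosts and 10 million cells per vial (preparation chart, section 10.2).

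Vials = boosts × cells per visit ÷ cells per vial

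- Lower end: 3 × 10 ÷ 10 = 3
- Upper end: 3 × 50 ÷ 10 = 15

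This is exactly the stated 3–15, so the stock agrees with a range read as the total per visit.

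**2. Apply the per-line rule.** Cells per visit = 10 million × lines. Vials = 3 × lines. The largest number of lines considered is one per screened peptide: 3 + 3 + 2 = 8.

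| Lines | Cells per visit (million) | Within 10–50? | Vials for three boosts | Within 3–15? |
|---|---|---|---|---|
| 1 | 10 | yes | 3 | yes |
| 5 | 50 | yes | 15 | yes |
| 6 | 60 | no | 18 | no |
| 7 | 70 | no | 21 | no |
| 8 | 80 | no | 24 | no |

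Two to four lines also fit (20–40 million, 6–12 vials). At eight lines the excess is 80 − 50 = 30 million, or 30 ÷ 50 = 60% of the stated maximum. By syringe under section 10, MBP holds at most 3 × 10 = 30 million and MOG/PLP at most (2 + 3) × 10 = 50 million.

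**3. Compare the two rules for syringe content.**

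| Lines available | Section 9.4 (one protein per syringe) | Section 10 (MBP; MOG and PLP pooled) |
|---|---|---|
| MBP with MOG, or MBP with PLP | can be followed | can be followed, same content |
| MOG and PLP, no MBP | separate syringes | both in one syringe, none for the other |
| All three proteins | impossible with two syringes | can be followed |
| One protein only | content of the second syringe not stated | no lines for one syringe |

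The rules therefore disagree for any patient with both MOG and PLP lines. Section 10 leaves one syringe without lines for every single-protein patient. The Protocol's own background (section 3.3) suggests that such patients occur: in one cited study 12 of 24 patients reacted to MOG, and 8 of those 12 to MOG exclusively. That study used purified antigens, not this panel of peptides, so it is an illustration and not an estimate for this trial.

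**4. Compare the volumes.** Synopsis: 1.5–3 ml for the whole dose. Section 10: 2 syringes × 1.5–3 ml = 3–6 ml per visit. Preparation chart: 1–3 ml. The synopsis and section 10 meet only at 3 ml. The chart's lower limit is below that of both.

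**The case against.** The strongest reply is that the dose statements form one coherent scheme. One to five lines at 10 million each give 10–50 million per visit, and three frozen boosts then need exactly 3–15 vials. The vial count could even be read as an implied ceiling of five lines. Sections 10.1 and the chart also speak of selected peptides, and some screened peptides overlap (MBP 83–99 with 87–110, PLP 184–199 with 190–209), so six or more injected lines may be uncommon. A dose range is an acceptable choice for an autologous product, and the earlier studies described in section 3.3 used ranges or a fixed number of cells per clone.

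Much of this stands. The agreement up to five lines is real, and the frequency of six or more lines is unknown. But a ceiling that has to be deduced from a vial count is not a rule: section 10 has no cap, whereas the per-clone study described in section 3.3 is reported with a maximum of six clones. The conflicts over syringe content and volume are untouched by this reply.

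A reader might infer more than the text supports:

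- *The three dose statements can never hold together.* They do for one to five lines.
- *Two syringes double the dose, to 20–100 million per visit and 6–30 vials.* Each line goes into one syringe only, the section 9.4 table gives one cell count per visit, and the stock matches only a per-visit total.
- *The injected volume may be 1 ml.* The phrase "then resuspended in 1 ml of PBS or saline and stored at 4oC" in section 10.3 describes processing and storage the day before injection.
- *The blind is compromised.* The synopsis gives placebo the same volume range and calls for matching injections, and section 10.5 requires identical covered tubes.

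**Conclusion.** The point holds in limited form. The stated range, the per-line rule and the vial stock agree for up to five lines. For six to eight lines the per-line rule gives 60–80 million cells per visit against a stated maximum of 50 million, and 18–24 vials against a stated maximum of 15. Whatever the line count, sections 9.4 and 10 disagree on syringe content for a patient with both MOG and PLP lines, a single-protein patient has no lines for one of section 10's two syringes, and the volume per visit is 1.5–3 ml, 3–6 ml or 1–3 ml depending on the passage.

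The figures for six to eight lines assume at most one injected line per screened peptide, and that only the three boosts are drawn from the frozen stock, as the chart says. Section 10.6 does not exempt the first dose from thawing. A reader might therefore infer that all four doses come from the stock, giving 30–150 million ÷ 4 = 7.5–37.5 million per visit, but the chart's three frozen injections do not support that. The documents do not show how many patients would be affected. No sample size, power or significance level is involved.

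**What to change.** Reconcile the synopsis (Study Objectives, Route and Dosage Form, Treatment Arms), section 9.4, the opening paragraph of section 10 and the preparation flow chart so that one definition applies throughout. The text should state:

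- whether 10–50 million cells and 1.5–3 ml are totals per visit or amounts per syringe, using *injection* in one sense only;
- how the per-line figure and the range fit together when a patient has more than five lines;
- which lines go into which syringe;
- what the second syringe holds for a patient reactive to one protein only.

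The number of frozen vials, and the placebo volume and number of syringes, should then be aligned with that definition. Which figure or rule applies is for the sponsor to decide.

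The cost is amendment wording. No patients, visits or procedures are added.

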**10.1 Isolation of PLP, MBP and MOG peptide T-cell lines for the T-cell vaccination**

PLP, MBP and MOG peptide-reactive T cells will be isolated from the MS patients with the identical methods used for the generation of antigen specific T-cell lines described previously (20). On visit 2, fifty milliliters of peripheral blood will be drawn from MS patients, supplemented with 10 IU/ml heparin. PBMC will be isolated by Ficoll Paque as described above. PBMC will be washed twice with RPMI (GIBCO, USA).The cells will be plated out in 96 well U-bottom plates (Nunc, Roskilde, Denmark) at a density of 100,000 cells per well in the presence of 5-20 µg/ml of PLP, MBP and MOG peptides (Chiron USA or Severn biotech ,Germany). On day 7, 50 ml of peripheral blood will be drawn (visit 3) from MS patients, supplemented with 10 IU/ml heparin. PBMC will be isolated by Ficoll Paque as described above and will be prepared as pulsed APC’s. On day 7, cultures will be restimulated with the autologous irradiated (7,000 rad) PBMC (100,000 cells per well) used as pulsed APC in the presence of the peptides selected, followed by the addition of 5 U/ml rIL-2 (Cetus or Boehringer Manheim approved for human use) after 48 hours. On day 15, all cultures will be tested for their reactivity to the PLP, MBP and MOG peptides in a proliferation assay by measuring the amount of [3H]-thymidine incorporation. Positive wells will be considered those in which reactivity to the antigen is at least two times above the background.

## To generate PLP MBP or MOG-specific T-cell lines, positive wells will be collected and restimulated with irradiated autologous PBMC and peptide antigens as described above (visit four). Restimulation will be performed at weekly intervals. PLP, MBP, MOG peptide specific T-cell lines will be restimulated and expanded (visits 5 to 7) to sufficient numbers for 4 injections. The Culture medium

The culture medium will contain RPMI with autologues serum supplemented with 1% Sodium-Pyruvate, 1% L-Glutamine (200 mM Seromed, Berlin Germany), ), gentamicin. (20µg/ml)

10.2 Freezing protocol

Aliquots of ten million cells per 1 ml freezing media (Cosmic calf serum (HYCLONE) certified for human use and 10% DMSO) will be freezed (-190C in liquid nitrogen) and stored for future injections.

**10.3 Cell inactivation**

One day prior to the injection date, if indicated by the results of functional tests, the cells will be washed and incubated in culture medium at 10-15 x 106 cells/ml irradiated at 6,000 RAD and then resuspended in 1 ml of PBS or saline and stored at 4oC.

10.4 The following characteristics of these PLP, MBP and MOG peptide-reactive T-cell lines will be evaluated prior to the injection:

1. Expression of TCR ab or TCR-gd and CD4 or CD8 by flow cytometry.

2. The fine specificity of the T-cell lines will be examined in a proliferation assay (18), including PLP, MBP and MOG peptides as described above (see screening procedure).

3. Determination of cytokine profile; the presence of IL-2, IL-4, IL-10, IFN-g and TNF-a in the supernatants of unstimulated and antigen-activated (with PLP, MBP and MOG peptides) will be analyzed by sandwich ELISA (19).

4. Quality Control (QC) tests for microbiological, mycoplasma and endotoxin contaminations will be performed 2-3 days prior to injection.

**10.5 TCV labeling and packaging**

The TCV and the placebo will be packed in identical tubes that are covered to prevent distinguishing between the two groups. The label on the tube will specify the patient number and date.

**10.6 Storage**

The T-cell lines will be stored in liquid nitrogen-190C and thaw, washed and irradiate one day prior to administration day. The dead T-cell will be stored in appropriate tubes at 4oC.

**10.7 Quality Control and Assurance of TCV Preparations**

A. Microbiology tests: two days prior to the cell injection, negative and positive gram stain assays will be performed and broth culture done to detect contaminations. Bacteriological contaminations will be tested using TSB (soya been broth test) for aerobic and TIOH (thio-glycolate broth test) for anaerobic. Agar blood will be used only for positive TSB and/or TIOH tests. The microbiology test will be performed at Hadassah Hospital in the Microbiology laboratory.

B. Mycoplasma and endotoxin: Contaminations for mycoplasma and endotoxin will be tested three days prior to the cell injection. In addition, a viability test will be performed before the cell irradiated and only cultures containing 50% or greater viable cells will be used for treatment.

C. Validation of the irradiated cells or viability: validation studies of the radiation source and the viability of the PBMC's will be performed to establish the performance of the irradiator. The cobalt60-radiation device at the Radiation Unit in Hadassah will be validated once a year. In addition, T-cell viability test will be performed once in three month starting from the beginning of the study. The cell viability will be study by monitoring the proliferation competence of the cell in response to mitogenic stimuli *in vitro*. Specifically, peripheral Blood Mononuclear Cells (PBMC’s) will be purified from a healthy-donor blood using Ficoll gradient. Ten million cells in one milliliter will be irradiated with 2000 rad, 4000 rad, 6000 rad or 8000 rad. The irradiated cells will be cultured (2x106 cells/ml) in RPMI supplemented with 10% autologous serum and 0.3µg/ml PHA for 24 hours. The cells viability will be monitor by H3 -Thymidine uptake assay for 4 hours. This assay measures the incorporation of thymidine into the cell's DNA as result of cell division and DNA replication. Furthermore, viability frequency of the irradiated cell will measured by flow cytometry analysis (FACS) using propidium iodide (PI) staining. This procedure takes advantage of the FACS FL2 detector to recognize dead cells that incorporate the red fluorochrome propidium iodide into cellular DNA. Briefly, Irradiated cells (1x105) will be treated with PI (1µg/ml) and immediately will be analyze by FACScan (Becton Dickinson). The frequency of dead cell will be determined.

D. In our facilities, special care has been taken to prevent contaminations (GMP facility for the T-cell cultures). QC microbiological tests such as TSB and TIOH broth cultures, endotoxin, and mycoplasma tests will be performed prior to the injections. All peptides (Severn Biotech) would be made to a high purity of in excess of 95% purity, typically 99% by HPLC and verified by Mass spectrometry. (MALDi-TOF) and follow ISO9000 principles of manufacturing. Materials (Citus for r-IL2) will be GLP-approved for human injection. Culture media will be serum-free or will contain autologous serum.

